##### Sample Size Considerations

As an example, we calculated the sample size required to examine changes in body weight. Conservatively assuming a 2-year weight loss of 33% for surgical patients with a standard deviation of 17%,[18,27] a 25% 2-year difference in weight between surgical patients and intensively treated medical controls (an extremely conservative estimate, as this difference is generally several orders of magnitude),[18,27] a 2-sided α = 0.05, β = 0.9, and 30% attrition rate, we would require 13 patients.

#### Comparisons of Costs Over Three Years Between the Surgical Arm, Medically Treated Controls and Wait-listed Controls

First, descriptive statistics will be used to assess cumulative and incremental costs (by perspective and cost category) in each year using the arithmetic mean and 95% confidence interval for normally distributed variables and median with interquartile ranges for skewed variables. Within and between-group comparisons will be performed. Distributions of cost are often skewed and will be normalized, if necessary, by using log-transformations. Unadjusted analyses of costs will be performed using ANOVA; if cost cannot be normalized then nonparametric (e.g., Kruskal-Wallis) tests will be used. If log-transformation of costs is necessary, Duan's smearing estimator will be used to calculate appropriate error estimates after the data are re-transformed from the logarithmic scale [63].

Second, covariate controlled sequential multiple linear regression models will be constructed to determine the independent association of surgery (versus medical or wait-list controls) on each incremental cost outcome. Cumulative costs over time will be calculated using standardized methods,[64,65]and costs for average hypothetical patients will be calculated using the least squares means method, and adjusted for significant predictor variables for costs for medical and wait-listed controls.

Third, the net economic impact of increasing bariatric surgery rates from a societal, public payor, and health care payor perspective will be assessed using a mathematical model developed by our team. The costs determined above will be input, and the net economic impact of increasing rates of bariatric surgery from current rates (0.1% of eligible patients) to 0.5% (estimated current rates in US), 5% and 10% of all eligible patients will be calculated.

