## Abstract

**Background:**

Extreme obesity affects nearly 8% of Canadians, and is debilitating, costly and ultimately lethal. Bariatric surgery is currently the most effective treatment available; is associated with reductions in morbidity/mortality, improvements in quality of life; and appears cost-effective. However, current demand for surgery in Canada outstrips capacity by at least 1000-fold, causing exponential increases in already protracted, multi-year wait-times. The objectives and hypotheses of this study were as follows: 1. To serially assess the clinical, economic and humanistic outcomes in patients wait-listed for bariatric care over a 2-year period. We hypothesize deterioration in these outcomes over time; 2. To determine the clinical effectiveness and changes in quality of life associated with modern bariatric procedures compared with medically treated and wait-listed controls over 2 years. We hypothesize that surgery will markedly reduce weight, decrease the need for unplanned medical care, and increase quality of life; 3. To conduct a 3-year (1 year retrospective and 2 year prospective) economic assessment of bariatric surgery compared to medical and wait-listed controls from the societal, public payor, and health-care payor perspectives. We hypothesize that lower indirect, out of pocket and productivity costs will offset increased direct health-care costs resulting in lower total costs for bariatric surgery.

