## Objectives and Hypotheses

The APPLES study is a population-based, prospective controlled study enrolling at minimum of 500 patients and designed to assess the impact of extended wait-times for bariatric care and examine the clinical and cost-effectiveness of bariatric treatment in the Canadian context.

The three major objectives of APPLES are:

1. To assess the impact of extended wait times for bariatric care by examining the two-year change in clinical, economic and humanistic outcomes in wait-listed patients. We hypothesize that patients will report progressive deterioration in these outcomes over time.

2. To determine the clinical effectiveness and changes in health-related quality of life associated with modern bariatric procedures and compare these outcomes to medically treated controls and untreated wait-listed controls. We hypothesize that surgery will markedly reduce body weight, decrease the need for unplanned medical care, and increase quality of life compared to controls.

3. To compare the costs associated with bariatric surgery to costs associated with medical and wait-listed controls over three years, from societal, public payor, and health care payor perspectives. We hypothesize that lower indirect, out of pocket and productivity costs will offset increased direct health-care costs resulting in lower total costs for bariatric surgery.

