4. **Impact of Extended Wait Times: **The Waiting List Impact Questionnaire (WLIQ),[53] is a previously validated 47-item list of open-ended patient statements designed to assess the impact of extended wait-times in Canada for coronary bypass surgery and will be administered to wait-listed patients. This instrument has been modified for use in a bariatric population and items deemed not relevant to the bariatric setting were eliminated, resulting in a 40-item questionnaire. The instrument assesses general quality of life on a scale of 0-100 and also examines specific domains (physical stress, social support, frustration, employment status), which are serially evaluated by patients on a 5-point Likert scale. The degree of interest in bariatric surgery is specifically assessed.

5. **Edmonton Obesity Staging Score (EOSS)**:[54] EOSS is a recently proposed, preliminary staging system for obesity which is based upon the presence or absence of obesity-related comorbities. EOSS will be evaluated as a triage and prognostic tool within the APPLES cohort.

6. **Economic Data **(Table 1): Economic data will be collected for the year prior to enrolment and in the two years following enrolment. Two major data sources will be used to collect economic data.

a. **Administrative Data**: Linkage to AHS and Alberta Health and Wellness (AHW) administrative data sources will be performed according to previously described methods [55,56]. Because all permanent residents of Alberta are eligible for insurance by AHW and over 99.9% participate in this coverage, these administrative data will comprehensively capture patient-specific health care resource utilization. Data elements include vital statistics (mortality) and the following health care resources and costs: inpatient and outpatient encounters, physician billings, medical procedures, and emergency room visits (Table 1).

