##### Sample Size Considerations

Using previous estimates,[66] we have adequate power to detect a difference of 20% or greater in costs between the surgical groups and the medical controls or the wait list controls, assuming an average 2-year total incremental cost of $12 183 in surgical patients, a standard deviation of $6000, two sided alpha = 0.05, and beta = 0.90.

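### The cost comparison is framed over three years, one of them before enrolment, but is powered on a two-year cost; the outcome window, time zero and the meaning of incremental cost need to be fixed

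*Protocol article*

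**What the plan says.** The abstract sets the third aim as "To conduct a 3-year (1 year retrospective and 2 year prospective) economic assessment of bariatric surgery compared to medical and wait-listed controls". Objective 3, under Objectives and Hypotheses, is "To compare the costs associated with bariatric surgery to costs associated with medical and wait-listed controls over three years", with the hypothesis that total costs will be lower with surgery. The heading of the cost analysis repeats the window: "Comparisons of Costs Over Three Years Between the Surgical Arm, Medically Treated Controls and Wait-listed Controls". The Economic Data item under Data Collection and Outcome Measures confirms where the third year lies: "Economic data will be collected for the year prior to enrolment and in the two years following enrolment".

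The analysis text is less definite than the heading:
- In the first step, "descriptive statistics will be used to assess cumulative and incremental costs (by perspective and cost category) in each year", followed by comparisons within and between groups.
- In the second step, regression models with covariates are fitted "to determine the independent association of surgery (versus medical or wait-list controls) on each incremental cost outcome". Incremental is not defined, and prior-year cost is not named among the covariates.
- In the third step, the resulting costs feed a model of raising surgery from 0.1% of eligible patients to 0.5%, 5% and 10%.

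The sample-size paragraph for costs claims that "we have adequate power to detect a difference of 20% or greater in costs", "assuming an average 2-year total incremental cost of $12 183 in surgical patients". The Discussion also describes the time frame of data collection as two years.

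**The concern.** The year before enrolment is inside the window over which the groups are to be compared, and the hypothesis attached to that window is causal. The groups are not randomised. A difference in prior-year cost would mainly reflect who reaches surgery, medical care or the wait-list, yet a three-year total would credit it to surgery.

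The groups could plausibly differ in that year. Under Eligibility For Surgery, clinic patients receive about 24-36 weeks of intensive counselling, during which surgical candidates are assessed. Under Study Setting and Subject Recruitment, wait-listed patients receive only community group education. Clinic visits are a counted cost (Table 1, category 5). Table 1 refers the administrative costs to a time zero that the text at hand does not define for each group. Figure 1 is not shown, so it may say more.

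At stake are the main economic contrast and the policy projections that take its costs as input.

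**Working it through.** **1. The plan's own power figure.** Inputs from the cost sample-size paragraph: mean $12,183 over two years, SD $6,000, two-sided alpha 0.05, and beta = 0.90 read as 90% power. Group sizes from Overall Study Design: 150 surgical, 200 medical, 150 wait-listed. The 20% is taken of the surgical mean (an assumption).

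- Difference: 0.20 × 12,183 = $2,436.6.
- Number per group for 90% power: 2 × (1.960 + 1.282)² × (6,000 / 2,436.6)² = 128 after rounding up.
- Power = Φ(2,436.6 / SE − 1.96), with SE = 6,000 × √(1/n₁ + 1/n₂).
- 150 vs 150: SE = 692.8, ratio 3.517, power 94.0%.
- 150 vs 200: SE = 648.1, ratio 3.760, power 96.4%.

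The claim is confirmed for a two-year cost at full enrolment.

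**2. How the prior year enters the contrast.** Let F be mean cost over the two follow-up years and P mean cost in the prior year, for surgery (S) and a control group (C).

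- Three-year total: (F_S − F_C) + (P_S − P_C). The prior-year difference is added in full.
- Change from the prior year, one possible meaning of incremental: the prior-year difference is subtracted.
- Each year taken separately: the prior-year comparison stands alone and describes selection.

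The readings therefore use the same year with opposite signs or not at all. As an illustration, suppose prior-year cost differed by 10% of $12,183, which is $1,218.3. That is 1,218.3 / 2,436.6 = half of the difference the study is sized to detect. The documents give no value for the prior-year difference, so neither its size nor its direction is known.

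**3. Power if the prior year were summed in.** The documents give neither the prior-year SD nor its correlation with later cost. Assume a prior-year SD of k × $6,000 with k from 0.5 to 1.0, correlation ρ from 0 to 0.5, and an unchanged effect of $2,436.6. The three-year SD is 6,000 × √(1 + k² + 2ρk).

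| k | ρ | Three-year SD | 150 vs 150 | 150 vs 200 |
|---|---|---|---|---|
| 0.5 | 0 | $6,708 | 88.2% | 92.0% |
| 0.5 | 0.5 | $7,937 | 75.8% | 81.1% |
| 1.0 | 0 | $8,485 | 70.1% | 75.8% |
| 1.0 | 0.5 | $10,392 | 52.8% | 58.4% |

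**4. Prior year as covariate for the two-year outcome.** The residual SD is 6,000 × √(1 − ρ²). At ρ = 0, 0.3 and 0.5, power is 94.0%, 95.8% and 98.2% for 150 vs 150, and 96.4%, 97.6% and 99.1% for 150 vs 200. At full enrolment, keeping the prior year out of the outcome is enough to meet the stated power, and the covariate adds to it.

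**5. Where the clinic pathway may fall.** If time zero for surgical patients is close to surgery, 24-36 weeks of clinic care could fill 24/52 = 46% to 36/52 = 69% of their prior year. If time zero is at clinic entry, the same cost falls in follow-up. The text shown does not say which applies.

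**The case against.** The strongest reply is that the protocol never says the three years are added into one outcome. It describes costs by year, plans within-group comparisons that would naturally set the earlier year against the later ones, and models an incremental cost that could mean change from the prior year. The two-year power basis and the Discussion's two-year time frame can be read as showing that the outcome is two-year cost, with the retrospective year as reference. The models already adjust for covariates, nothing excludes prior cost, and an article need not list every covariate.

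Much of this stands. A reader might infer that the plan definitely counts the prior year as outcome, but the analysis text does not support so firm a statement. The absence of a covariate list is not itself a fault. What remains is that the objective, abstract and heading all fix a three-year between-group comparison, and no sentence says what the prior year is for.

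A reader might also infer that the stated power is lost and that the covariate would restore it. It is not lost: the figure is already for two years and is met. Bringing in the 30% attrition used for quality of life and weight would give 83.7% (105 vs 105) and 88.2% (105 vs 140) for the two-year outcome, and covariate adjustment would then reach 90% only with a correlation of about 0.42 or 0.24. The cost paragraph states no attrition, however. Categories 1, 2, 3 and 5 come wholly or partly from administrative data, with over 99.9% insurance participation and more than 96% linkage in earlier work, so 30% loss is doubtful for those costs.

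**Conclusion.** The point holds as a mismatch and an undefined outcome: a three-year comparison that includes a pre-enrolment year, a two-year power basis, and an undefined incremental cost. If the objective is followed as written and the years are accumulated, the bias equals the prior-year cost difference between groups, which the documents do not give. In that case power would be about 53-88% (150 vs 150) or 58-92% (150 vs 200), given the assumed SD ratio, correlation and unchanged effect. For the two-year outcome the stated power stands at full enrolment.

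It would be too strong to call the prior year free of treatment. If surgical time zero lies near surgery, that year contains clinic-pathway cost. Dropping it would hide part of what surgery costs, and adjusting for it would adjust away part of the exposure. The remedy below allows for this.

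**What to change.** - State time zero for each of the three groups.
- Define the primary cost outcome as total cost in the two years after time zero, and define incremental or drop the word.
- Report the retrospective year by group as a baseline description.
- Prespecify prior-year cost as a covariate in the adjusted cost models.
- Show clinic-pathway cost before time zero (Table 1, category 5) separately, and exclude it from the baseline covariate.
- Reword objective 3, the abstract and the section heading to two years adjusted for the prior year, matching the power basis.
- Feed the policy model from this two-year contrast, with the pathway cost visible beside it.

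The cost is wording and one covariate built from data already being collected. The small downside is the extra work of separating pathway cost, and the need to settle time zero before the prior year is used for adjustment.

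### For skewed costs the plan switches to medians and to log-scale or rank tests, although the hypothesis, the power statement and the impact model all concern arithmetic mean cost

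*Protocol article*

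**What the plan says.** Objective 3 (Protocol article, Objectives and Hypotheses) expects that savings elsewhere will "offset increased direct health-care costs resulting in lower total costs for bariatric surgery".

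The section on comparing costs over three years sets out the analysis:

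- **Description:** "arithmetic mean and 95% confidence interval for normally distributed variables and median with interquartile ranges for skewed variables".
- **Skewness:** "Distributions of cost are often skewed and will be normalized, if necessary, by using log-transformations".
- **Unadjusted tests:** "Unadjusted analyses of costs will be performed using ANOVA; if cost cannot be normalized then nonparametric (e.g., Kruskal-Wallis) tests will be used".
- **Retransformation:** if logs are used, "Duan's smearing estimator will be used to calculate appropriate error estimates after the data are re-transformed from the logarithmic scale".
- **Adjusted analysis:** "covariate controlled sequential multiple linear regression models will be constructed to determine the independent association of surgery", with least squares means for average hypothetical patients. Whether these are fitted on dollars or on logs is not stated.
- **Net-impact model:** the resulting costs are inputs to a model of raising surgery rates from 0.1% to 0.5%, 5% and 10% of eligible patients.

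The sample size paragraph that follows claims adequate power for a 20% difference, given an average two-year surgical cost of $12,183 and an SD of $6,000.

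**The concern.** A total cost is the arithmetic mean per patient multiplied by the number of patients. A median, a geometric mean or a rank does not multiply up in that way. Yet for skewed costs, which the section itself says are common, the stated summary is the median and the stated unadjusted test is on logs (geometric means) or on ranks.

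When the arms have the same spread on the log scale, this matters little, because the ratio of geometric means equals the ratio of means. When spreads differ, the log and rank tests can reject although mean costs are equal, miss a real saving, or point the wrong way. The stake is practical: the Discussion says that clear cost savings or neutrality from the public payor perspective would show surgery to be dominant and make its expansion a priority.

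**Working it through.** **1. The plan's own figure.** Inputs from the cost sample size paragraph: mean $12,183, SD $6,000, two-sided alpha 0.05, and the stated beta of 0.90 read as 90% power. The difference is 0.20 × 12,183 = $2,436.60. Treated as a comparison of arithmetic means:

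n per arm = 2 × [(1.960 + 1.282) × 6,000 / 2,436.60]² ≈ 127.4, so 128.

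With the planned group sizes and no attrition, power is 94% (150 v 150) and 96% (150 v 200). The claim reproduces as a statement about arithmetic means.

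**2. Where medians and means part.** Assume lognormal costs. The surgical CV is 6,000 / 12,183 = 0.492. The lognormal median, which is also the geometric mean, is mean / √(1 + CV²):

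- Surgery: 12,183 / √(1 + 0.492²) = $10,929.
- Control, if surgery is truly 20% cheaper: mean 12,183 / 0.8 = $15,229. At CV 1.0 the median is 15,229 / √2 = $10,768, already below surgery. At CV 1.5 it is 15,229 / √3.25 = $8,447.

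The order reverses once the control CV exceeds √[(15,229 / 10,929)² − 1] = 0.97. The protocol gives no control CV, so it is varied below as an assumption.

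**3. Simulation.** Two-group comparisons, 150 v 150, lognormal costs, two-sided 0.05, 4,000 runs per row, surgical arm fixed at $12,183 and SD $6,000. Lognormal data would follow the plan's log branch. The rank test (two-group Kruskal-Wallis) is shown beside it.

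Equal true means:

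| Control CV | Log test: surgery dearer | Rank test: surgery dearer | Unequal-variance t on dollars: any rejection |
|---|---|---|---|
| 0.49 | 2.5% | 2.4% | 4.9% |
| 0.75 | 39% | 38% | 5.3% |
| 1.0 | 86% | 84% | 6.6% |
| 1.5 | 99.9% | 99.6% | 7.5% |

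Surgery truly 20% cheaper (control mean $15,229), runs significant for cheaper / dearer:

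| Control CV | Log test | Rank test | Unequal-variance t on dollars |
|---|---|---|---|
| 0.49 | 98% / 0% | 98% / 0% | 97% / 0% |
| 0.75 | 38% / 0% | 36% / 0% | 85% / 0% |
| 1.0 | 1.4% / 3.7% | 1.5% / 3.9% | 66% / 0% |
| 1.5 | 0% / 76% | 0% / 73% | 32% / 0.1% |

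**4. Whether smearing repairs it.** Take control mean $15,229 and CV 1.5. The group smearing factors are √(1 + 0.492²) = 1.115 for surgery and √3.25 = 1.803 for control. Applied by group they return the true means: 10,929 × 1.115 ≈ $12,183 and 8,447 × 1.803 ≈ $15,229. A single pooled factor, (1.115 + 1.803) / 2 ≈ 1.459, gives about $15,940 for surgery and $12,320 for control, which is still the wrong order. The protocol does not say which form is meant.

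**The case against.** The case on the other side has real force.

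- **The plan is not confined to medians and ranks.** A reader might infer that it offers no way back to mean dollars. It does not go that far: smearing, covariate-adjusted regression and least squares means stand in the same section and can yield average costs. What remains is that smearing is described only as supplying error estimates, leaves the test itself on the log scale, does not apply to Kruskal-Wallis, and needs group-specific factors when spreads differ. The regression helps if fitted on dollars, but its scale is open.
- **No test is named as primary for Objective 3.** A reader might take the ANOVA or Kruskal-Wallis step to be the main economic test. The protocol calls it unadjusted, and in a non-randomised cohort the adjusted model is the more natural basis for inference.
- **The median rule belongs to the descriptive step.** Medians are useful description. The fault is that the mean is not also reported for skewed totals.
- **The harm needs unequal spread.** The only CV that the protocol supports is 0.49, for surgery. Surgical costs may have a long tail of their own: Risks of Surgery cites immediate complications in 10% and band slippage (6%) or erosion (10%) leading to re-operation, and three different operations are performed. With CV 1.0 in both arms and surgery 20% cheaper, nothing reverses, and the log and rank tests have more power (about 63% and 61%, against 49% for the test of means).

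Unequal spread is still plausible. Every surgical patient incurs an operation, while wait-listed patients receive no specific intervention beyond group education sessions.

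**Conclusion.** The point holds as a mismatch between question and analysis that should be fixed. The section states rules that, for skewed costs, summarise and test something other than the mean cost that the hypothesis, the power statement and the impact model require. The smearing and regression steps soften this without settling it.

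The size depends on the lognormal form and on a control CV that the protocol does not give. With equal means, the log and rank tests wrongly call surgery dearer in about 40%, 85% and over 99% of runs at control CV 0.75, 1.0 and 1.5. With equal CVs there is no reversal. A reader might infer that the trial's cost conclusion will come out with the wrong sign. The documents do not support that: they show only that it can happen if control costs are appreciably more dispersed than surgical costs.

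**What to change.** In the cost-comparison section:

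1. Report the arithmetic mean cost per patient with a 95% confidence interval (for example bootstrap) for every cost total, whatever the skew. Medians and interquartile ranges can stand beside it.
2. Base the Objective 3 comparison and the impact-model inputs on the surgical-minus-control difference in arithmetic means. Unadjusted, use a bootstrap or unequal-variance comparison. Adjusted, use any model that returns mean dollars, such as a generalised linear model with log link, or log regression with group-specific smearing.
3. State the scale of the adjusted regression, and describe smearing as an estimator of the retransformed mean.
4. Keep log-scale ANOVA and Kruskal-Wallis as supportive analyses.

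This changes analysis wording only and needs no new data. The cost is precision: under heavy skew the intervals widen, and in the control CV 1.5 case above the test of means has only about 32% power for a true 20% saving. That limit should be acknowledged when the cost results are interpreted.

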### Data Collection and Outcome Measures (Additional File 1 and Table 1)

**Table 1 T1:** Cost categories and details of source data for quantification and valuation of relevant costs

**Cost Category**^**1**^	Source Details	Units of Resources	Time Frame
1. Inpatient encounters	Administrative data	# of hospitalizations length-of-stay	Provided by fiscal year Referenced to time zero
2. Outpatient encounters	Administrative data	# encounters # procedures	Provided by fiscal year Referenced to time zero
3. Physician Fees	Administrative data	# encounters Provider specialty Service provided	Provided by fiscal year Referenced to time zero
4. Medications	Patient interview	Name Dosage, frequency & duration	Bi-annual
5. Weight Wise Clinic Visits	Administrative data and chart review	Personnel (nurses, dieticians, support staff) salaries Administrative and capital costs Supplies & equipment	Provided by fiscal year Referenced to time zero
6. Home Care & Long Term Care	Patient interview	Personnel (nurse, OT, PT, RT) salaries Disability aids (walker, bars, rails, etc.) Administrative and capital costs	Bi-annual
7. Transfer Payments	Patient interview	Unemployment insurance Disability benefits Assured Income for the Severely Handicapped (AISH)	Bi-annual
8. Employment status, absenteeism	Patient interview	Employment status in past year (# hours/week, # weeks) Absenteeism in past year (# days) Annual income (by quintile)	Bi-annual
9. Weight Loss Interventions	Patient interview	Weight loss program, meal replacements, physical trainer, exercise programs, alternative therapies, nutritional counselling, commercial program	Bi-annual
10. Mobility and Medical	Patient interview	Mobility aids, home modification/renovations, rehabilitation, paid personal assistance (household activities and home productivity, driving)	Bi-annual
11. Personal/Household Productivity	Patient interview as part of quality of life surveys	Capacity to perform household/domestic activities, personal care, and participate in leisure activities (Scalar) Paid/unpaid caregivers	Bi-annual

AHCIP = Alberta Health Care Insurance Plan. MACAR = Morbidity and Ambulatory Care Abstracting Record. DAD = Discharge Abstract Database. LOS = Length of stay. CIHI = Canadian Institute for Health Information. OT = occupational therapy. PT = physiotherapy. RT = respiratory therapy. SW = social worker.

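### The log rule for skewed costs makes no provision for zero costs in the adjusted category-level or single-year models; perspective totals are largely unaffected

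*Protocol article*

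**What the plan says.** The section on cost comparisons over three years begins with descriptive statistics for "cumulative and incremental costs (by perspective and cost category) in each year". For skew it names one transformation: "Distributions of cost are often skewed and will be normalized, if necessary, by using log-transformations". Unadjusted comparisons use ANOVA, with a fallback: "if cost cannot be normalized then nonparametric (e.g., Kruskal-Wallis) tests will be used". If logs are used, "Duan's smearing estimator will be used to calculate appropriate error estimates after the data are re-transformed from the logarithmic scale".

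For the adjusted comparison, "covariate controlled sequential multiple linear regression models will be constructed" to estimate the "independent association of surgery (versus medical or wait-list controls) on each incremental cost outcome". That paragraph does not state the scale of the outcome and gives no fallback.

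Table 1 lists eleven cost categories. They include inpatient encounters, "Home Care & Long Term Care", transfer payments, and mobility and medical items. The setting section says that wait-listed patients are expected at community education sessions and otherwise receive nothing specific. This implies zeros for specialty-clinic visits while they wait. The footnote to Table 1 builds the three perspective totals by summing categories 1-6, 1-7 or all of them.

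**The concern.** The log of zero is undefined. An analyst who applies the stated skew rule to a category with zeros must drop the zero-cost patients or add a constant. Dropping them compares users with users. Adding a constant lets an unstated choice set the answer. Smearing corrects retransformation bias and does nothing about zeros. If incremental means change from the pre-enrolment year, some values may also be negative, and the log fails there too.

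Three things are at stake. The study is not randomised, so the adjusted models carry more weight than the unadjusted tests. Objective 3 sets lower indirect, out-of-pocket and productivity costs against higher direct costs, which is a statement about components, and components are where zeros fall. The third step of the cost analysis feeds the estimated costs into a net-impact model, which needs arithmetic mean cost per patient with non-users counted.

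**Working it through.** **1. The plan's own cost figure.** The sample size text for costs gives a mean of $12,183, SD $6,000, a 20% difference, two-sided alpha 0.05 and 90% power (written there as beta).

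- Difference: 0.20 × 12,183 = $2,436.60.
- n per arm = 2 × (1.960 + 1.282)² × 6,000² / 2,436.60² = 127.4, so 128.
- This is within the 150 planned. Power is 0.940 for 150 v 150 and 0.964 for 150 v 200, without attrition.

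The figure reproduces. It concerns untransformed totals, so the zero problem does not touch it.

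**2. Inpatient illustration.** The inputs are assumptions, because the article gives no admission rates: 150 per arm; all surgical patients admitted, mean $10,000, CV 0.5; 15% of controls admitted, mean $10,000, CV 1.0; lognormal costs among users.

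- True means: $10,000 and 0.15 × 10,000 = $1,500. Difference $8,500, ratio 10,000 / 1,500 = 6.7.
- Mean log cost among users = ln(mean) − ½ ln(1 + CV²). Surgical: 9.2103 − 0.1116 = 9.0988. Control: 9.2103 − 0.3466 = 8.8637.
- Users-only ratio: exp(9.0988 − 8.8637) = 1.265, from about 0.15 × 150 = 22.5 controls.
- log(cost + $1): exp(9.0988 − 0.15 × 8.8637) = exp(7.7692), about 2,370.
- Simulation medians (2,000 replicates): difference $8,531, ratio of means 6.87, users-only 1.26, and 2,380, 47.8 and 7.3 for added constants of $1, $100 and $1,000.

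Range over the assumed control admission rate:

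| Controls admitted | True ratio (1/rate) | Users-only | log(cost + $1) |
|---|---|---|---|
| 10% | 10 | 1.27 | exp(9.0988 − 0.886) ≈ 3,690 |
| 15% | 6.7 | 1.27 | ≈ 2,370 |
| 25% | 4.0 | 1.27 | exp(9.0988 − 2.216) ≈ 975 |

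The users-only ratio does not move, because it ignores who incurs a cost.

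**3. Smearing does not rescue it (15% case).**

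- Users only: geometric means are 10,000/√1.25 = $8,944 and 10,000/√2 = $7,071. The pooled smearing factor is (150 × 1.118 + 22.5 × 1.414)/172.5 = 1.157. The difference is (8,944 − 7,071) × 1.157 ≈ $2,170, against a true $8,500.
- log(cost + $1): the control geometric mean of cost + 1 is exp(0.15 × 8.8637) = 3.78, and its mean exponentiated residual is 1,501/3.78 ≈ 397. The pooled factor is (397 + 1.118)/2 ≈ 199. The surgical mean becomes about 8,945 × 199 ≈ $1.78 million (simulation median about $1.7 million), against a true $10,000.

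**4. A less extreme category.** Assume $3,000 per user in both arms, log-SD 1.2, and a surgical user share 0.6 times the control share. The true ratio is 0.60. The mean log cost among users is ln 3,000 − 0.72 = 7.286.

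| Control zeros | Users-only | +$1 | +$100 | +$1,000 |
|---|---|---|---|---|
| 20% | 1.0 | exp(−0.32 × 7.286) = 0.10 | 0.41 | 0.71 |
| 50% | 1.0 | exp(−0.20 × 7.286) = 0.23 | 0.57 | 0.81 |
| 80% | about 1.0 | exp(−0.08 × 7.286) = 0.56 | 0.80 | 0.92 |

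No single constant recovers 0.60 across the rows.

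**5. Direction can reverse.** Take a surgical user share 0.7 times and a cost per user 1.6 times that of controls. The true ratio is 0.7 × 1.6 = 1.12 and the users-only ratio is 1.6. The log(cost + k) ratio lies below 1 for every constant tried, from $0.01 to $1,000 (0.08 to 0.98).

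**The case against.** The strongest reply is that the article does not commit to the faulty analysis. Much of that reply stands.

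- A reader might infer that category costs are certain to be logged and regressed. The log is conditional, and the paragraph on adjusted models does not mention logs. Linear regression in dollars is open under this wording and handles zeros. What remains is that the log is the only remedy named for skew, and smearing is a step that follows a log-scale model, so a logged regression is a natural reading.
- A reader might infer that most categories are mainly zeros. No zero share is given. Physician fees, outpatient encounters and medications are probably non-zero for most of these patients. The supportable word is several.
- A reader might infer that the conclusion on total cost is compromised. Objective 3 ends in lower total costs, the power statement concerns totals, and even the narrowest perspective sums six categories. Totals will rarely be zero.
- Category-level regression is itself partly an inference. The words on perspective and category attach to the descriptive statistics, and the regression is said only to be "on each incremental cost outcome".
- For the unadjusted test there is a route, since a category with a spike at zero cannot be normalised and goes to the nonparametric test. That test does not estimate mean cost, but it is at least defined.
- Handling of zeros may be set out in a fuller plan that is not shown. Its absence from an article is no fault. The point made here is narrower: the skew rule that the article does state fails on outcomes that the article itself lists.

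**Conclusion.** The concern holds in a conditional form. If the log is carried into adjusted models for a cost category, or for a single year, that contains zeros, the result is a users-only comparison or one set by the added constant. Neither is mean cost per patient.

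Under the assumed inpatient inputs, a true ratio of 4 to 10 becomes about 1.27 among users, or roughly 975 to 3,690 with $1 added. In other assumed cases the direction reverses. These figures show the mechanism and do not predict the study's results: admission rates, user shares, means and spreads are all assumed, and inpatient cost is an extreme category because every surgical patient has an index admission.

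The perspective totals, the stated power for them and the hypothesis on total cost are largely unaffected. The change is worth making because objective 3 contrasts cost components and because the net-impact model needs arithmetic means.

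**What to change.** State in the paragraph on adjusted cost models that no cost outcome containing zero or negative incremental values will be log-transformed. For such outcomes, estimate the adjusted difference in arithmetic mean cost per patient, zeros included, on the dollar scale with a bootstrap confidence interval. For non-negative category costs with enough users in each arm, a two-part model may be used instead: logistic regression for any cost, then a gamma generalised linear model with log link for positive cost, recombined into mean cost per patient in each arm with a bootstrap interval for the difference.

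This needs no further data or patients, only wording and slightly more analysis work. The two-part model may be unstable where few controls are users (about 22 of 150 in the illustration), and its gamma part does not apply to negative values. The dollar-scale estimate is the safer choice in both cases.
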